## Methods

### Overview of Study Design

This pilot feasibility study will use a 1-way within-subjects repeated-measures design to examine changes in walking and stationary behaviors across the 3 time periods: baseline, just-in-time, and JITAI. This study will consist of a preintervention measurement session, followed by a 2-week observation period that will serve as a baseline for walking and stationary behaviors, a 2-week just-in-time learning period, a 2-week JITAI period, and concluding with a postintervention measurement session (Figure 1). The receptiveness-in-context data from the just-in-time learning period will be used to train and individually adapt the JITAI server by learning the ideal contexts in which the participants are most receptive to each of the 3 intervention notifications, as detailed in the Architecture of the WWJ App and Server section.

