### Analytic Plan, Sample Size, and Power Estimates

#### Data Processing

The WWJ server will store all data for manual processing. Data processing will start by ensuring all timestamps for walking and stationary bouts are sequentially aligned. This alignment will allow for accurate calculations for transitions between these states and other activity modes. Outliers, including device-specific artifacts, such as overlapping timestamps and erroneous bout durations such as those too short to be meaningful (eg, <10 seconds) or exceeding physical limits (eg, >5 hours of continuous walking) and walking speeds surpassing human capacities (eg, >3 m/s) [40], will be identified and reviewed for manual correction or exclusion. Additionally, geographic locations tagged in the data and any nonadherence responses marked as “other” and inputted by participants will be downloaded and coded using an inductive approach to group similar entries into cohesive categories emerging organically from the data. Once fully processed, all data will be stored in a standardized format.

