#### Analytic Plan

Using the latest version of JMP Statistical Software (currently JMP, version 19.01, SAS Institute Inc, 1989-2025), preliminary analyses will include baseline descriptive statistics and exploratory data analysis. Baseline characteristics of the participants (eg, self-reported MVPA minutes from the screener, demographics, behavior change constructs, anthropometrics, and resting vital signs); recruitment, enrollment, and retention rates; implementation fidelity; adherence and compliance rates; user-burden; acceptability; treatment-specific expectations of benefits and preferences will be summarized in frequency tables for categorical variables and means and SDs for quantitative variables. Qualitative responses to applicable feasibility notifications and open-ended exit surveys will be explored.

Walking behavior and stationary time measures through all 3 periods—baseline, just-in-time, and JITAI—support a 1-way within-subjects ANOVA analysis of continuous measures (eg, average bout duration, speed, distance, and stationary time per study period for each participant) to demonstrate the feasibility of effecting a change in the behavior profile throughout the WWJ study. The intended 1-way within-subjects ANOVA assumes limited outliers, normality, and sphericity, which will be assessed graphically using boxplots, the Shapiro-Wilk test, and Mauchly test, respectively. Outliers, if present, will be assessed for their potential to weaken the analysis and removed if necessary. Nonnormal data will be transformed using the Box-Cox procedure to achieve normality. If sphericity is violated, the Greenhouse-Geisser and Huynh-Feldt corrections will be used. Tukey post hoc testing will be used to explain the differences between WWJ periods. If normality cannot be approximately achieved, the nonparametric Friedman test will be used. The model will be extended to allow for covariates if data screening of other collected demographic measures (eg, education) suggests their importance.

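### Walking and stationary records are to be corrected or excluded by hand under example limits only, and outliers removed for weakening the analysis; uneven handling between periods could not be told from a period effect

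*Protocol article*

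**What the plan says.** The Data Processing section of the protocol article opens with "The WWJ server will store all data for manual processing". It names the kinds of artefact to look for: overlapping timestamps, bouts "too short to be meaningful (eg, <10 seconds"), bouts "exceeding physical limits (eg, >5 hours of continuous walking"), and "walking speeds surpassing human capacities (eg, >3 m/s"). All three numbers are examples. Records so identified "will be identified and reviewed for manual correction or exclusion". The section does not say when a record is corrected rather than excluded, or what value a correction takes.

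The Analytic Plan adds a second step on the data entering the ANOVA: "Outliers, if present, will be assessed for their potential to weaken the analysis and removed if necessary".

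The cleaned bouts are averaged per participant and per study period, and those averages are compared. The Overview of Study Design describes a "1-way within-subjects repeated-measures design to examine changes in walking and stationary behaviors across the 3 time periods": baseline, just-in-time and JITAI, in that order for everyone and with no concurrent control.

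**The concern.** Both steps are discretionary and both act on outcome data. In the first, a person decides whether a flagged bout is edited, dropped or kept. In the second, the criterion is what the value does to the analysis, not whether it was mismeasured.

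The person cleaning the data can probably tell which period a bout belongs to. The article does not say so; it is an inference from three things. "Data processing will start by ensuring all timestamps for walking and stationary bouts are sequentially aligned". The periods follow one another in fixed order, so a date gives the period. No masking is stated.

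With one group and no control, a difference in handling between periods has the same form as a behaviour change. Initial impact on walking and stationary behaviour is among the primary aims, the sample size was calculated for it, and the Strengths and Limitations section expects the effect sizes to inform a later randomized trial. A cleaning artefact would therefore carry forward.

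**Working it through.** **Inputs from the article.** Three repeated measures, within-subject correlation 0.5, alpha 0.05, Cohen f = 0.32, power 0.80, 17 participants needed, 15% attrition, 20 planned (Sample Size and Power Estimates); final sample 18 (Results).

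**The plan's own figure.** For a one-group repeated-measures ANOVA, λ = f²·n·m/(1−ρ), with df1 = m−1 and df2 = (n−1)(m−1). At n = 17, λ = 0.1024 × 17 × 3/0.5 = 10.44 and power is 0.794. At n = 18 it is 0.820. The stated 17 is reproduced to within one participant, and 17/0.85 = 20. The sample size is not in question.

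**How much a cleaning-induced shift would matter.** Assume no true effect and handling that shifts one period's mean by d standard deviations (between-person SD within a period). Then f = d√2/3, so at n = 18, λ = (2d²/9) × 18 × 3/0.5 = 24d².

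| d | λ | Rejection rate (nominal 5%) |
|---|---|---|
| 0.1 | 0.24 | 6.7% |
| 0.2 | 0.96 | 12.2% |
| 0.3 | 2.16 | 22.4% |
| 0.5 | 6.00 | 54.4% |

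The reverse also holds. The planned f = 0.32 equals one period differing by 0.32 × 3/√2 = 0.68 SD. At n = 17, handling that takes away 0.1, 0.2 or 0.3 SD lowers power from 79% to 65%, 48% or 32%.

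**Could bout-level handling produce such shifts?** A simulation with no true effect and n = 18 assumed 40 real walking bouts per participant and period (median 8 min) plus fragments under 10 s making up 10%, 20% or 30% of all records. None of these rates is in the article.

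| Handling of fragments | 10% | 20% | 30% |
|---|---|---|---|
| All removed in every period | 4.4% | 5.0% | 4.7% |
| None removed in any period | 3.9% | 4.9% | 4.6% |
| All removed in JITAI, half removed elsewhere | 7.6% | 17.3% | 40.6% |

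The inflation comes only from unevenness. Uniform removal and uniform retention are both harmless to the error rate.

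**One long artefact.** Suppose a participant has k recorded walks in a period, all of 10 min except one 4-hour artefact. The period mean is (10(k−1) + 240)/k: 21.5, 17.7 or 13.8 min for k = 20, 30 or 60. Spread over 18 participants, the group period mean moves by 11.5/18 = 0.64, 7.67/18 = 0.43 or 3.83/18 = 0.21 min, which is about 6%, 4% or 2% of 10 min.

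**The case against.** Hand review of sensor artefacts is ordinary practice, and a condensed article may leave the cleaning rules, the masking and the log to a data management plan. No text says that handling will differ by period, and the simulation inflates the error rate only by assuming that it does, with artefact rates that the article does not give. The Walking and Stationary Behaviors section says behaviour is recorded once thresholds are met (250 m of walking or 30 minutes stationary), so records under 10 s may be plain artefacts with little room for judgement. The Analytic Plan also provides boxplots, a Box-Cox transformation and a Friedman fallback, which dampen isolated extremes. The Strengths and Limitations section puts feasibility and acceptability first.

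Much of this stands. Period visibility is inferred, uneven handling is not shown, and the size is unknown. A reader might infer from the 4-hour example that one keep-or-drop decision moves the trial result by 77% (10.0 to 17.7 min with 30 walks). It does not: that is one participant's period mean, and the group mean moves by about 4%. Nor would fixing the limit at the example value of 5 hours remove that artefact; open-ended human review might catch it.

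The stated method does not fall with these points. The article does more than leave detail out: it specifies manual correction or exclusion of outcome records, and then removal by effect on the analysis. Transformation and ranks tame a stray value, but they do not remove a shift that runs through many participants in one period.

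**Conclusion.** The point holds as a weakness in a stated procedure, with a cheap improvement available. The plan combines case-by-case editing under non-binding limits with an outlier rule tied to the analysis, in a comparison where unequal handling and a period effect cannot be told apart.

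The size cannot be given from the article. The rejection rates above are conditional on an assumed shift or on assumed artefact rates and unequal removal. They show that modest unevenness would matter with 18 participants, not that any occurred. A reader might go further and conclude that the cleaning is known to be unmasked, or that the results cannot be interpreted. The documents support neither: masking is unstated, and evenly applied review would leave the error rate near its nominal level.

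According to the Results section, data collection is complete and the analyses are still to be finished, so the change may still be possible.

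**What to change.** Before the period comparison is run:

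- Fix the bout-level limits, including a maximum walking duration low enough to catch implausibly long walks, and apply them by script identically in all three periods. Removing a period label would mask nothing while timestamps remain; the protection comes from the identical rule.
- Exclude flagged bouts instead of editing their values by hand. Allow only rule-based, logged repair of overlapping timestamps.
- Report the numbers of exclusions and repairs by period and by outcome.
- Replace the Analytic Plan's outlier rule: keep participant-level outliers in the main analysis unless they are documented measurement errors.
- Add one sensitivity analysis with no discretionary edits or removals, in which a script excludes impossible records only. A rerun on wholly raw records would bring back overlapping timestamps and impossible speeds and would say little.

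The cost is a short script, one table and one extra run, with no new data. The downside is that a few bouts which hand review could have rescued are lost, and some artefacts inside the limits are kept.

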#### Analytic Plan

Using the latest version of JMP Statistical Software (currently JMP, version 19.01, SAS Institute Inc, 1989-2025), preliminary analyses will include baseline descriptive statistics and exploratory data analysis. Baseline characteristics of the participants (eg, self-reported MVPA minutes from the screener, demographics, behavior change constructs, anthropometrics, and resting vital signs); recruitment, enrollment, and retention rates; implementation fidelity; adherence and compliance rates; user-burden; acceptability; treatment-specific expectations of benefits and preferences will be summarized in frequency tables for categorical variables and means and SDs for quantitative variables. Qualitative responses to applicable feasibility notifications and open-ended exit surveys will be explored.

Walking behavior and stationary time measures through all 3 periods—baseline, just-in-time, and JITAI—support a 1-way within-subjects ANOVA analysis of continuous measures (eg, average bout duration, speed, distance, and stationary time per study period for each participant) to demonstrate the feasibility of effecting a change in the behavior profile throughout the WWJ study. The intended 1-way within-subjects ANOVA assumes limited outliers, normality, and sphericity, which will be assessed graphically using boxplots, the Shapiro-Wilk test, and Mauchly test, respectively. Outliers, if present, will be assessed for their potential to weaken the analysis and removed if necessary. Nonnormal data will be transformed using the Box-Cox procedure to achieve normality. If sphericity is violated, the Greenhouse-Geisser and Huynh-Feldt corrections will be used. Tukey post hoc testing will be used to explain the differences between WWJ periods. If normality cannot be approximately achieved, the nonparametric Friedman test will be used. The model will be extended to allow for covariates if data screening of other collected demographic measures (eg, education) suggests their importance.

During implementation, communication drops or a lack of participant adherence may result in missing observations in some instances that inform the planned ANOVA. It will therefore be necessary to explore missing observations as to missing completely at random, missing at random, and missing not at random by using missing data analytics in JMP to associate instances with other study conditions (eg, software considerations and behavioral context). To the extent that the structure leading to the missing observation is not present or identifiable, missing at random or missing completely at random will be assumed for those records, and a linear mixed model will be used, leveraging maximum likelihood for estimation to achieve the within-subjects ANOVA goals without case-wise deletion. Missingness will be summarized in the analysis.

Secondary analyses will examine the initial effectiveness of the walking and stationary prompts. Specifically, the success or failure of notifications to encourage walking (ie, walking faster or longer) or reduce stationary time (ie, registered walking for at least 1 minute). Interarrival times and bouts of walking and stationary times computed at baseline will be summarized in terms of location and spread for continuous values or as frequency tables for bouts of activity.

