### Objective, Aims, and Research Questions

This protocol paper presents the development of the “Walking With Just-in-Time Adaptive Interventions” (WWJ) iPhone and AW app, server, and methodology for a 6-week pilot study among adults who are not meeting the 2020 WHO PA recommendations. The primary aims of the WWJ’s study are to examine the feasibility and initial impact of a 2-week JITAI approach for increasing walking behavior (ie, walking speed, distance, and duration) and decreasing stationary behavior (ie, duration of SB and idle standing) compared to a 2-week baseline observation period and a 2-week just-in-time learning period. Thus, our corresponding research questions include: (1) Is the WWJ feasible, regarding recruitment, retention, intervention fidelity, acceptability, adherence, and engagement? (2) To what extent does the just-in-time approach impact walking and stationary behavior compared to baseline? (3) How do changes in walking and stationary behaviors across a 2-week just-in-time and a 2-week JITAI approach compare to baseline?

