**Figure 2 figure2:**
[figure not shown]
WWJ architecture per agent. AW: Apple Watch; WWJ: Walking With Just-in-Time Adaptive Intervention.

The context analyzer synthesizes external (eg, weather and calendar) and internal (eg, GPS coordinates mapped to tagged locations) contexts into a current context feature vector. At decision points, these contextual features (detailed under “contextual variables”) are used in binary classification models to determine whether an intervention notification should be sent based on the predicted likelihood of successful behavior change within these contexts as processed and interpreted by the learner module. Thus, 3 decision trees (policies) will be trained for each user corresponding to the intervention notification types (Figure 3)—walk faster (ie, “You should pick up the pace”), walk longer (ie, “Let’s make it a longer walk”), and stand up and move around (ie, “It’s time to move around for one minute”).

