**Figure 3 figure3:**
[figure not shown]
The WWJ intervention notifications: walk faster, walk longer, and stand up. WWJ: Walking With Just-in-Time Adaptive Intervention.

The learner module (Figure 2) also establishes baseline walking and stationary behaviors during the initial 2-week observation period by passively monitoring behaviors and calculating their applicable averages (eg, average walking speed) per bout. During the just-in-time learning period, intervention notifications are triggered at each instance that participants meet a predetermined threshold for walking and stationary behaviors—unless they have marked themselves as “busy” on their calendar to not burden the user during unsuitable times such as work meetings. The threshold for the walking notifications is set at 250 m from the initial start point of a walking detection. This distance was chosen after trial-and-error field testing among 4 authors ([name], AV, KD, and [name]), which indicated that walking less than 250 m from a given starting location may not align with viable opportunities to walk faster or longer. The WWJ application will send a “walk longer” notification if the system recognizes that the user is in or near a previously tagged location. In all other cases, participants will receive a “walk faster” notification. When stationary behavior is detected for 30 continuous minutes, the application will send the “stand up and move around” notification. The system will determine if these interventions are successful or not (ie, receptiveness) either by comparing the current behaviors in the just-in-time learning period to those in the observation period within the same contexts for walking behavior or by the AW detecting that the user got up and walked around for a minute for stationary behavior. As shown in Figure 2, data collected by the executor during the just-in-time learning period serves as labeled training data to compute and optimize personalized prompting policies for the JITAI period. At the end of the just-in-time learning period, the learner module uses this labeled data to generate a decision-tree–based policy, predicting when and when not to send the intervention notifications to the user based on their current context, past receptiveness, and predicted support needs. As predicting behavior is uncertain, the learning model will deliberately use intervention notifications even if the user may not be receptive, with a 10% chance of such occurrences, to allow behavior change in previously nonoptimal contexts and for the system to learn continually.

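### Walking is analysed as period averages with no total, so short walks from the stand-up prompt either can pull the averages down while walking rises or are not counted

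*Protocol article*

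**What the plan says.** The aims and research questions concern "increasing walking behavior (ie, walking speed, distance, and duration) and decreasing stationary behavior (ie, duration of SB and idle standing". They do not say whether this means per bout or in total. Sample Size and Power Estimates calls change in walking behavior and stationary time the primary outcomes.

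The Analytic Plan gives as examples of the ANOVA measures "average bout duration, speed, distance, and stationary time per study period for each participant". The Architecture section describes the learner's baseline in the same style: "calculating their applicable averages (eg, average walking speed) per bout". No section names total walking time or distance per day or per period. For bout counts, the only statement is that "Interarrival times and bouts of walking and stationary times computed at baseline will be summarized".

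On the stand-up prompt, the Architecture section says: "When stationary behavior is detected for 30 continuous minutes, the application will send the" stand-up message, whose text includes "time to move around for one minute". The secondary analyses score success as "registered walking for at least 1 minute". The observation period has no prompts (WWJ Observation Period, Just-in-Time, and JITAI Periods), and the number of prompts is not capped (Principal Findings).

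Three places bear on which walks reach the data:
- Walking and Stationary Behaviors makes collection conditional on a threshold. The only walking threshold given is 250 m (Architecture).
- Strengths and Limitations repeats 250 m as the minimum for detecting walking bouts that offer a chance to walk faster or longer.
- Data Processing gives about 10 seconds as an example of a bout too short to keep.

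**The concern.** Three kinds of prompt act on one walking record. Two try to make an existing walk faster or longer. The third tries to create a short walk where there was none. A mean over bouts responds to both the length of walks and their mix, so a prompt that adds short walks can lower the mean while participants walk more. Stand-up prompts are absent at baseline and present in both later periods, so the change in mix would coincide with the comparisons in research questions 2 and 3. Bouts per day in each period would reveal it, but the article names bout summaries only for baseline.

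The alternative recording rule creates the opposite gap: if walks below 250 m are never collected, the walking outcomes cannot see the minimum response this prompt asks for.

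Strengths and Limitations intends the effect sizes to inform the size of a later randomized trial. A walking effect that can move against walking volume is a poor basis for that.

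**Working it through.** **The plan's own figure.** The sample size is not in dispute. With f = 0.32, correlation 0.5, three measures and α = 0.05, power at 17 participants is 0.794, close to the stated 0.8, and 17/0.85 = 20.

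**Step 1: can a one-minute walk reach 250 m?** It would need 250/60 = 4.17 m/s, above the 3 m/s that Data Processing treats as beyond human walking. In 60 seconds a participant covers 49-53 m at 0.82-0.89 m/s and 78-108 m at 1.3-1.8 m/s (paces from the Background). A prompted walk would have to last 250/1.8 = 139 s to 250/0.82 = 305 s to reach 250 m. Under a 250 m collection rule, the minimum successful walk therefore adds nothing.

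**Step 2: does the cleaning rule point the other way?** Even at 3 m/s, 250 m takes 250/3 = 83 s. A floor of about 10 seconds has little purpose unless much shorter bouts are stored. Scoring stand-up success also needs a one-minute walk to be registered. This implies, without proving, that short walks are in the data.

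**Step 3: effect on the mean if short walks count.** Let B be usual walks per day, D their mean length, k prompted walks per day and P their length.
- Mean after = (B×D + k×P)/(B + k)
- Total after = B×D + k×P

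The mean falls only if D exceeds P. The total rises whenever the prompted walks are additional. The documents give none of B, D or k, so all are assumptions. For scale, the Background cites about 8 sedentary hours a day, which at one prompt per 30 stationary minutes allows at most 16 prompts. With P = 1 min:

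| B | D | k | Mean after | Change in mean | Total per day |
|---|---|---|---|---|---|
| 10 | 5 min | 4 | 54/14 = 3.86 min | -23% | 50 to 54 min (+8%) |
| 4 | 10 min | 5 | 45/9 = 5.0 min | -50% | 40 to 45 min (+12.5%) |
| 10 | 2 min | 5 | 25/15 = 1.67 min | -17% | 20 to 25 min (+25%) |
| 10 | 1 min | 5 | 15/15 = 1.0 min | 0% | 10 to 15 min (+50%) |
| 20 | 45 s | 5 | 20/25 = 0.80 min (48 s) | +7% | 15 to 20 min (+33%) |

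At a common pace, mean distance changes by the same percentages.

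**Step 4: a longer prompted walk.** One minute is a minimum. With P = 3 min in the first row, the mean is (50 + 12)/14 = 4.43 min (-11%) and the total 62 min (+24%). The fall is smaller, but the two measures still move in opposite directions.

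**Step 5: how much lengthening would offset it?** In the first row, the usual walks would need to reach (14×5 - 4)/10 = 6.6 min, 32% longer, for the mean to stay at 5.0 min.

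**The case against.** The strongest reply is that the recording rule, read literally, excludes walks below 250 m, in which case there is no dilution. That stands as far as it goes: a fall in the averages is possible, not shown. But on that reading the one-minute walks drop out of the walking outcomes, so the problem changes form.

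Other replies have weight:
- The measures are listed as examples, the word bout attaches directly only to duration, and the article condenses a fuller protocol. Even so, every walking example is an average, and no total appears where the aims are stated.
- If bouts just over 10 seconds count, the usual bout may itself be short, and the mean may not move or may rise (last two rows of the table).
- Participants also get up unprompted at baseline, so a prompt may bring a walk forward instead of adding one.
- Stationary time, this prompt's direct target, is in the same ANOVA, and prompt success is examined separately. Walk-longer prompts may offset the dilution. A reader might infer that success with the stand-up prompt will read as harm; the documents do not support that.
- The article puts feasibility first and defers a powered test to a later trial. That lowers the stakes but does not remove research questions 2 and 3.

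Three further inferences should be resisted:
- **Average speed must fall.** No section gives the pace of prompted walks. With assumed paces of 0.85 against 1.2 m/s, the unweighted bout mean is (10×1.2 + 4×0.85)/14 = 1.10 m/s (-8%). Distance over time is (50×1.2 + 4×0.85)/54 = 1.17 m/s (about -2%). At equal pace there is no change.
- **JITAI is artificially favoured over just-in-time.** Halving successes from 4 to 2 would raise the mean from 3.86 to 52/12 = 4.33 min (+12%) while the total falls from 54 to 52. But the policy prunes prompts predicted to fail, and nothing supports a halving of successes.
- **A period with no walk is treated as missing.** The article attributes missing data to communication drops and nonadherence and does not say this.

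**Conclusion.** The point holds in conditional form. The article names only averages as walking outcomes and leaves open whether walks below 250 m enter them. If they do, mean bout duration and distance can move against total walking: -23% against +8% in the illustration. This requires usual bouts longer than the prompted walk and prompted walks that are additional. If they do not, the walking created by a minimum successful stand-up response is not counted. Either way the named walking outcomes do not reliably answer whether participants walk more.

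The percentages rest on assumed walk counts and lengths and are not predictions. Effects on speed and on the JITAI versus just-in-time contrast remain possibilities, not demonstrated errors.

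**What to change.** 1. Reconcile Walking and Stationary Behaviors and Strengths and Limitations (250 m) with Data Processing (about 10 seconds). State one definition of the analysed walking bout and apply it identically in all three periods.
2. Add total walking time and total distance per worn day (or worn hour) as period outcomes in the within-subjects analysis.
3. Report per-bout duration, distance and speed for walks reaching 250 m, the walks eligible for a walking prompt.
4. Report bouts per day in every period, not only at baseline.
5. If walks under 250 m were not stored, say that the totals cover only walks of 250 m or more, and do not enter zero as if no walking had occurred.

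The Results section says data collection is complete and analyses are pending, so this can still be fixed beforehand. If short walks were stored, the cost is wording and re-aggregation of timestamped bouts. If not, totals over all walking cannot be rebuilt and the stated limit is the remedy. The downside is slightly more analysis, with per-bout averages read alongside totals.

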### Sample Size and Power Estimates

Power calculations for the planned 1-way ANOVA were performed using G*Power Version 3.1.9.6. [34]. With 3 collapsed times of repeated measures (baseline, just-in-time, and JITAI) and assuming a within-subject correlation of 0.5, given the focus on feasibility for this study, the most effective sample size for predicting our primary outcomes (change in walking behavior and stationary time) was 17 participants with an α level of 0.05, medium-to-large effect size of Cohen f=0.32, and power of 0.8. Allowing for 15% attrition due to dropout or adherence issues, our proposed sample size is 20 participants.

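### The Friedman fallback drops anyone who lacks a whole period, and the plan does not say whether it or the mixed model governs when data are both non-normal and incomplete

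*Protocol article*

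**What the plan says.** The Analytic Plan analyses one summary value per period and participant: "average bout duration, speed, distance, and stationary time per study period for each participant". The route is a one-way within-subjects ANOVA, then a Box-Cox transformation if the data are not normal, and then a last step: "If normality cannot be approximately achieved, the nonparametric Friedman test will be used". That sentence carries no condition about completeness.

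The next part of the same section turns to missing data. It expects that "communication drops or a lack of participant adherence may result in missing observations in some instances that inform the planned ANOVA". Where missingness at random or completely at random is assumed, it uses a linear mixed model, "leveraging maximum likelihood for estimation to achieve the within-subjects ANOVA goals without case-wise deletion".

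Sample Size and Power Estimates plans for losses: "Allowing for 15% attrition due to dropout or adherence issues, our proposed sample size is 20 participants". The underlying requirement is "17 participants with an α level of 0.05, medium-to-large effect size of Cohen f=0.32, and power of 0.8".

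**The concern.** Both triggers are foreseen. The plan provides for data that stay non-normal after transformation, and it provides for missing observations. It does not provide for the two together. On the ANOVA route, a participant who stops before JITAI still contributes baseline and just-in-time values. On the Friedman route, read literally, that participant disappears.

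A whole period could also be missing without dropout. Under Walking and Stationary Behaviors, data are collected once a threshold is reached, and the walking threshold is 250 m. Strengths and Limitations accepts that some participants may not reach it. On one reading, such a participant has no walking value for a period.

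What is at stake is selection. If people who respond poorly to just-in-time prompting are more likely to stop, the completers look better than the enrolled group. Research questions 2 and 3 concern exactly these comparisons with baseline.

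**Working it through.** **1. The plan's own figure.** Inputs from Sample Size and Power Estimates: n = 17, m = 3 periods, f = 0.32, α = 0.05, and "assuming a within-subject correlation of 0.5". Sphericity is assumed here.

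- λ = f²·n·m/(1−ρ) = 0.1024 × 17 × 3 / 0.5 = 10.44, with 2 and 32 degrees of freedom.
- Power = 0.794, which agrees with the stated 0.8.
- Attrition: 17/0.85 = 20, as stated. In reverse, 20 × 0.85 = 17.

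**2. The two rules side by side.**

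| Data | Rule stated | Participant lacking one period |
|---|---|---|
| Normal, complete | ANOVA | – |
| Normal, incomplete | Mixed model, maximum likelihood | Kept |
| Non-normal, complete | Friedman | – |
| Non-normal, incomplete | Not stated; the literal rule is Friedman | Dropped |

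**3. Bias in an extreme case.** Assumptions: 20 enrolled, three periods with SD 1 and correlation 0.5, normal errors and no true effect. The 3 participants with the lowest just-in-time minus baseline change leave before JITAI.

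- Variance of just-in-time minus baseline = 2(1 − 0.5) = 1, so its SD is 1.
- The three lowest of 20 standard normal values average about −1.87, −1.41 and −1.13, which sum to −4.41.
- The 17 completers therefore average 4.41/17 = 0.26 SD above zero on just-in-time minus baseline.
- Covariance of that change with JITAI minus baseline = ρ − ρ − ρ + 1 = 0.5. The regression slope is 0.5, so the false JITAI gain is 0.5 × 0.26 = 0.13 SD.

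**4. Rejection rate under no effect, by simulation (nominal 5%).**

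| Dropout before JITAI | Analysis | Rejection |
|---|---|---|
| 3 poorest responders | Friedman, 17 completers (normal, t3 or exponential errors) | 11–12% |
| Milder response-related dropout (mean 3.3 of 20) | Friedman, completers | 8% (false JITAI gain 0.09 SD) |
| Random | Friedman, completers | about 5% |
| 3 poorest responders | Skillings-Mack, all 20 | 5–6% |
| 3 poorest responders | Mixed model, all 20 (600 runs, normal errors) | 4.7% (false JITAI gain 0.02 SD) |

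The mixed-model result is as expected, because this dropout depends only on values that were observed.

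**5. Power on the fallback route.** n = 17, f = 0.32, ρ = 0.5, 20,000 runs, three patterns of period means. The error shapes are assumed.

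| Errors | Friedman | ANOVA |
|---|---|---|
| Normal | 0.63 | 0.79–0.80 |
| t3 | 0.87–0.88 | 0.83–0.84 |
| Exponential | 0.82–0.88 | 0.79–0.81 |

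**The case against.** The strongest reply is that the plan breaks no promise. The words about avoiding case-wise deletion belong to the mixed model and the ANOVA goals and do not cover every analysis. The section can even be read so that the mixed model takes over whenever data are incomplete and Friedman serves only complete, non-normal data. This stands as far as it goes: the two rules leave one combination unresolved and do not contradict each other. But the Friedman sentence has no such condition, and both rules are stated in the article, so the gap is not just detail left to a fuller plan.

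A reader might infer that the fallback loses 15% of the sample beyond what was planned. It does not. The 15% is the allowance that takes 17 to 20, and removing it returns the planned 17. It also combines dropout with adherence problems. Since the outcome is a period average, scattered missing days still leave a value. Only a wholly missing period removes someone, and the article does not say how many participants that would be. A participant with no usable data is lost under any method.

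A reader might also infer that Friedman falls short of the planned power. That holds only for normal errors, where Friedman would not be used. With the heavy-tailed and skewed errors tried, its power at n = 17 exceeds 0.8 and that of the ANOVA.

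Finally, the 11% comes from a constructed extreme. Strengths and Limitations treats the effect of burden on disengagement as unknown, and nothing in the article shows that poor responders leave. This stands, and the figure is an illustration only.

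**Conclusion.** The point holds as an unreconciled combination of rules. When data are non-normal and at least one participant lacks a whole period, the article gives two routes with different samples, and the literal one discards observed data. The harm depends on why people leave. With random dropout, the rejection rate stays near 5%. With dropout tied strongly to the just-in-time response, the false gains reach about 0.26 SD (just-in-time) and 0.13 SD (JITAI), with about 11% rejection. These sizes rest on the plan's correlation of 0.5, 20 enrolled, 3 leaving before JITAI and normal errors for the SD figures. They are not a prediction for this study. The article reports a final sample of 18 but not how many have all three periods.

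The matter is modest: it arises only if Box-Cox fails and a period is wholly missing, in a pilot focused on feasibility. It is still worth settling, because the article describes the analyses as not yet complete and the choice should not be made after seeing both results.

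**What to change.** Add to the Analytic Plan:

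- When any participant lacks a period, the maximum-likelihood mixed model, on the best available transformation, remains the analysis. It supplies the period contrasts with confidence intervals.
- Skillings-Mack replaces Friedman as the rank-based check. With complete data the two are identical, so nothing is lost there.
- The number of participants with all three periods is reported for each outcome.

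A participant-level bootstrap of the mixed model is optional. Its intervals tend to be slightly too narrow with about 18 participants.

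The cost is a few sentences and a little more analysis work, with no new data. Two limits should be stated. Skillings-Mack is strictly valid only when data are missing completely at random, and neither method cures missingness that depends on unobserved values.
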